## Abstract

**Background:**

Dendritic cells are professional antigen presenting cells with the ability, in their immature state, to induce tolerance in T cells. A protocol to develop phenotypically stable tolerogenic dendritic cells (TolDC) was developed in Newcastle and cells administered to participants in the phase I AuToDeCRA study, demonstrating that TolDC were safe and well tolerated. More knowledge of the TolDC product is now needed, such as optimal dose, route of administration and antigen loading. Establishing this and developing a biomarker profile to demonstrate favourable immunomodulation is the focus of AuToDeCRA-2.

**Methods:**

AuToDeCRA-2 is a non-commercial, phase IIa, 5-arm, randomised, unblinded, single-centre study. It is designed to demonstrate and compare immunomodulation achieved by TolDC administered via three distinct routes: intra-nodal, intra-articular, intra-dermal and, in the case of intra-nodal administration, at 2 doses. Participants will be randomised to one of these four active intervention arms or standard care. Participants in intervention arms will receive a single dose of TolDC loaded with synthetic citrullinated peptides (TolDC_CitPep_) representing disease relevant autoantigens. Twenty Anti-Citrullinated Peptide Antibody (ACPA) positive, shared epitope positive Rheumatoid Arthritis patients with nil-to-moderate disease activity will be randomised in an allocation ratio of 1:1:1:1:1.

Participants will be followed up with immune state monitoring performed on peripheral blood samples at baseline, 1, 3 and 6 weeks and lymph node aspirates at baseline and 1 week, alongside clinical assessment performed throughout and additionally at 12 weeks.

**Discussion:**

TolDC therapy is an emerging cellular therapy aimed at reversing the underlying abnormality in autoimmune disease by inducing tolerance to autoantigen. Expected challenges to this study include recruitment of potentially asymptomatic participants to a complex and intensive experimental medicine study. Limitations include the relatively small number of participants although adequate to address the aims of the study. Establishing acceptable route(s) of administration as well as demonstrating favourable immunomodulation via the development of a biomarker profile is the focus of AuToDeCRA-2, which aims to address some of the existing scientific gaps necessary for the development of TolDC therapy in autoimmune disease.

**Trial registration:**

ISRCTN, ISRCTN14999554. Registered on 27th September 2023.

## Administrative information

Note: the numbers in curly brackets in this protocol refer to SPIRIT checklist item numbers. The order of the items has been modified to group similar items (see http://www.equator-network.org/reporting-guidelines/spirit-2013-statement-defining-standard-protocol-items-for-clinical-trials/).

## Introduction

### Background and rationale {6a}

Autoimmune disease such as rheumatoid arthritis (RA) results from a breakdown of immunological tolerance; the immune system mistakenly recognises healthy, self-tissue as a threat, leading to inflammation and eventually structural damage. No current treatment option for RA represents a cure and medication is required indefinitely, carrying with it the risks of generalised immunosuppression. It is desirable to develop ‘tolerogenic’ treatments, which reverse the underlying abnormality of the immune system rather than continuous non-specific suppression of inflammation and immunity. Tolerogenic dendritic cells (TolDC) have emerged as one such possibility [1–7].

CD4^+^ helper T cells are a key driver of disease in RA, in keeping with their established role as orchestrators of adaptive immune responses through their interaction with professional antigen presenting cells (APC). As key APC, dendritic cells (DC) instruct CD4^+^ T cells how to respond to a given antigen by modulating the co-stimulation they provide. Depending on context, DCs can induce either proinflammatory or regulatory (tolerogenic) characteristics in the T cells [8]. If an antigen is encountered in the context of threat, the DC in question ‘matures’ and will present antigen with co-stimulatory signals, which leads to the generation of antigen-specific T cells with pro-inflammatory characteristics. Conversely, if the antigen is encountered in a non-threatening microenvironment, the DC remains ‘immature’ and upon interaction with the T cell, may induce a regulatory phenotype, anergy (a state of hyporesponsiveness) or even apoptosis. With their ability to influence the adaptive immune system in an antigen-specific way, DCs are an exciting potential therapeutic tool which could ‘reset’ autoimmunity.

Whilst immature DCs can induce T cell tolerance, their phenotype is unstable, and they may develop into immunogenic, mature DCs in the presence of pro-inflammatory cytokines. As such, a variety of protocols have been developed for the generation of phenotypically stable TolDC which retain their tolerogenic characteristics, even in a pro-inflammatory microenvironment. We have established such a protocol [9–12] and these cells were administered safely to patients with inflammatory arthritis in the earlier phase I AuToDeCRA study [1].

In AuToDeCRA, TolDC were loaded with autologous synovial fluid as a source of antigen and administered arthroscopically into an inflamed knee joint following saline wash-out. The lack of a subsequent disease flare following administration suggested that, as shown by in vitro studies, the TolDC phenotype was stable. These findings have been corroborated by several other international studies using TolDC in patients with RA and other autoimmune diseases such as multiple sclerosis and type 1 diabetes [3–7, 13]. Although no TolDC trial has yet demonstrated robust clinical efficacy, TolDC appear to be a safe and well tolerated intervention.

There is now a need to demonstrate the ability of TolDC to achieve immunomodulation. Tolerogenic therapies are not necessarily anti-inflammatory in the short term [14] and biomarkers of the immune state that are influenced more rapidly by such treatments are urgently needed, not least to guide clinical protocol development relating to aspects such as optimal dose, route of administration and antigen loading. AuToDeCRA-2 was developed to begin to address some of these questions.

### Objectives {7}

AuToDeCRA-2 is designed to demonstrate and compare immunomodulation using synthetic citrullinated peptide-loaded TolDC (TolDC_CitPep_) administered via three distinct routes: intra-nodal, intra-articular, intra-dermal and in the case of intra-nodal administration, at a low and a high dose. The rationale for loading TolDC with citrullinated peptides is explained in section ‘Intervention description {11a}’.

Table 1 outlines the study objectives which will be achieved by comparing baseline data with follow-up data at 1, 3, 6 and 12 weeks.

**Table 1 Tab1:** Study objectives

Primary objectives	Secondary objectives	Exploratory objectives
• To seek signals of immune modulation when TolDC_CitPep_ are administered to participants with RA using immune state biomarkers performed on peripheral blood samples at baseline, 1, 3 and 6 week follow-up and participant lymph node aspirates at baseline and 1 week follow-up	• To seek signs of clinical efficacy when TolDC_CitPep_ are administered to participants with RA using ACR 20, 50 and 70, DAS-28, and components thereof at baseline and 1, 3, 6 and 12 week follow-up • To provide further evidence of TolDC_CitPep_ safety using reported adverse events (AEs) at baseline, 1, 3, 6, and 12 week follow-up • To provide further evidence of participant acceptability of TolDC_CitPep_ therapy for RA using a Participant Acceptability questionnaire at 12 week follow-up	• To link signals of immune modulation with signs of potential efficacy of TolDC_CitPep_ using potential associations between immune modulation measures and evidence of efficacy for the three different routes of TolDC_CitPep_ administration (and, in the case of intra-nodal injection, for the two doses administered) • To compare intra-nodal (low and high dose), intra-dermal and intra-articular injection with regards to primary and secondary objectives, and feasibility

### Trial design {8}

AuToDeCRA-2 is a non-commercial, exploratory, unblinded, randomised experimental medicine study with 5 parallel groups of ACPA-positive RA participants in an allocation ratio of 1:1:1:1:1, with the aim of demonstrating and comparing immunomodulation by TolDC_CitPep_.

The study protocol follows the Standard Protocol Items: Recommendations for Interventional Trials (SPIRIT) 2013 statement. The study has been registered with ISRCTN [14999554].

## Methods: participants, interventions and outcomes

### Study setting {9}

The single-centre study will be undertaken at Newcastle upon Tyne Hospitals NHS Foundation Trust (NuTH) in the UK. All study visits will take place within a designated Clinical Research Facility at the Royal Victoria Infirmary, Newcastle upon Tyne, with the exception of leukapheresis visits which will take place in the Leukapheresis Day Unit at the Freeman Hospital, Newcastle upon Tyne.

### Eligibility criteria {10}

#### Inclusion criteria

Patients are eligible for the study if all of the following apply at screening:Adults aged 18 years old or overRA fulfilling 1987 ARA criteria or 2010 ACR/EULAR Classification CriteriaACPA > 3 × upper limit of normal, can include historical measurements providing the result remains positive at screeningAble and willing to give informed consent and to comply with the study protocolDisease duration of at least 4 months and less than 10 yearsACR Functional Class I-IIIDAS-28 < 5.1If receiving Disease Modifying Anti-Rheumatic Drugs, these can include any combination of methotrexate, sulphasalazine, azathioprine, hydroxychloroquine, abatacept, rituximab (last dose > 6 months ago), TNF-alpha inhibitors and IL6 receptor antagonists, provided stable dosing for at least 4 weeksPossess at least one copy of a shared epitope (SE) HLA DRB1 allele (0101; 0102; 0105; 0401; 0404; 0405; 0408; 0409; 0410; 0413; 0416; 0419; 0421; 1001; 1402; 1406; 1409; 1413; 1417; 1419; 1420; 1421)

#### Exclusion criteria

Patients are excluded from the study if any of the following apply at screening:Use of other investigational medicinal products within 30 days prior to study entry (defined as date of consent into study)Any changes to RA treatment within 4 weeks of study entryCurrent treatment with Janus kinase inhibitors or leflunomide. Previous treatment is permitted provided at least 12 weeks have elapsed at study entry since discontinuationReceiving glucocorticoids by any route within 4 weeks of study entry, apart from topical, intra-nasal or inhaledSerious or unstable co-morbidity that prohibits participation in the study at the discretion of the investigator, e.g. significant chronic obstructive pulmonary disease, significant cardiac failure, active malignancyActive infection at study entry (except fungal nail infection)Infection requiring hospitalisation or intravenous antibiotics within 4 weeks prior to study entryImmunisation with live, attenuated vaccines planned within 14 days of baseline visit (administration of TolDC_CitPep_) and with non-live vaccines planned within 7 days of baseline visitHistory of hepatitis B or C, HIV or HTLV-1/2 infection(s)Recent history of cytomegalovirus (CMV) infection (positive for CMV IgM antibodies) or syphilis infection (positive PCR test)Major surgery within 8 weeks prior to study entry or planned within 12 weeks of baseline visitPregnancy, or women planning to become pregnant within the study period, or women who are breast feedingFemales of childbearing potential engaging in heterosexual relationships unwilling to use adequate contraception for the duration of the studyPatients taking anticoagulants that cannot be interrupted and are, in the judgement of the investigator, likely to interfere with study proceduresKnown hypersensitivity to local anaestheticPoor venous access or medical condition precluding leukapheresis, e.g. unstable cardiac arrythmia (atrial fibrillation permitted)Haemoglobin < 10 g/dL; neutrophils < 1.00 × 10^9^/L; platelets < 100 × 10^9^/L

Radiologists performing ultrasound-guided lymph node aspiration and intra-nodal tolDC administration will be competent in the procedure.

Rheumatologists performing intra-articular administration will be competent at performing ultrasound guided intra-articular (knee) injection.

Clinicians performing intra-dermal administration will be competent at intra-dermal injections and have received training on the use of the specific intra-dermal needle selected for use.

### Who will take informed consent? {26a}

Following initial contact, and at least 24 h after provision of participant information documents, interested participants will attend a screening visit. At the screening visit, a member of the study team will ensure the participant information sheet (PIS) has been read and understood and answer any questions. If the participant wishes to enter the study, written informed consent will be obtained by a medically qualified member of the study team delegated to the task.

### Additional consent provisions for collection and use of participant data and biological specimens {26b}

There are 4 optional consent clauses which form part of the informed consent form (ICF) but do not affect eligibility to participate in the study.Agreeing to contact by the study team about participation in additional follow-up visits in the future, should additional research funding be obtained for these visits.Agreeing that any research samples remaining at the end of the study can be anonymised and sent to a biobank for long-term storage and use in future research outside of the study.Agreeing that any samples left over from TolDC manufacture can be anonymised and sent to a biobank for long-term storage and use in future research outside of the study.Agreeing to be sent a summary of the results when the study has finished.

## Interventions

### Explanation for the choice of comparators {6b}

The optimal route for TolDC administration is not clear. The DC-T-cell interaction is believed to occur primarily in lymph nodes. We hypothesise that the route of injection most likely to ensure the TolDC reach a lymph node is direct injection into lymph nodes, but intra-nodal injection is a less convenient route of delivery, requiring ultrasound equipment and a trained operator. AuToDeCRA-2 will therefore compare direct intra-nodal injection with alternative routes that should enable cells to reach disease-relevant lymph nodes. Intra-dermal is the most well studied route of administration [5, 6, 15] for therapeutic DC and does not require specialised equipment. In contrast, intra-articular injection requires specialised equipment and operators, but it is possible that the joint-relevant immune system is best accessed via this route. 10^7^ TolDC will be administered via all routes to provide a direct comparison, being the highest dose that was administered in AuToDeCRA. A lower dose of 10^5^ TolDC will also be administered intra-nodally as injecting directly into a lymph node may require fewer cells to achieve a therapeutic effect.

The fifth arm is standard care. Standard care was chosen over placebo so that participants would not need to undergo unnecessary leukapheresis or administration procedures. Standard care involves no leukapheresis visit and no administration of TolDC_CitPep_ but all other study procedures remain the same.

### Intervention description {11a}

Eligible participants will be randomised in equal proportions to one of four intervention arms or standard care. Participants’ usual medication will be continued alongside for all groups.

Participants randomised to an intervention arm will attend for leukapheresis at day − 8 to extract CD14^+^ monocytes for the generation of TolDC_CitPep_. Leukapheresis products will be transferred to Newcastle Advanced Therapies Good Manufacturing Practice (GMP) Facility where the TolDC_CitPep_ will be manufactured.

In AuToDeCRA and AuToDeCRA-2, TolDC manufacture is identical aside from the antigen loaded into TolDC. In AuToDeCRA-2, the TolDC will be loaded with synthetic citrullinated peptides (TolDC_CitPep_) representing disease-relevant epitopes [16–19] rather than autologous synovial fluid as in AuToDeCRA. Knowledge of the loaded antigen enables more sophisticated immune monitoring assays that incorporate measures of antigen specificity, allowing the profiling of the cells the treatment is designed to target. Furthermore, treatment is no longer limited to patients with a knee joint effusion, enabling treatment of participants with lower disease activity that may benefit most from tolerance inducing strategies. In vitro validation work has confirmed the immunological equivalence of AuToDeCRA and AutoDeCRA-2 TolDC.

TolDC_CitPep_ loaded with Cit-alpha-enolase (326–340), Cit-cartilage intermediate layer protein-2 (297–311), Cit-vimentin (59–78) and Cit-tenascin-C 22 (1012–1026) will be diluted to a final volume of 200 µl, aspirated into a syringe and undergo quality control and QP release. The syringe will be stored at 2–8 °C in a validated and monitored refrigerator until administration. Administration by all injection routes will be carried out immediately after (inguinal) lymph node aspiration (for biomarker analysis), following which participants will be observed for at least 90 min.
Intra-nodal injection of TolDC_CitPep_ (10^5^ or 10^7^ cells).TolDC_CitPep_ will be injected into up to 5 inguinal lymph nodes under ultrasound visualisation, on the ipsilateral side to the lymph node aspiration as per intra-nodal aspiration and injection Standard Operating Procedure (SOP).Intra-articular injection of TolDC_CitPep_ (10^7^ cells).TolDC_CitPep_ will be administered as a single injection into a knee joint under ultrasound visualisation as per intra-articular injection SOP. The knee selected should be the least inflamed, and ipsilateral to the aspirated lymph node where possible.Intra-dermal injection of TolDC_CitPep_ (10^7^ cells).
Intra-dermal injection will be administered as one or two injections to the upper, anterior thigh (within 5 cm of the inguinal crease) on the ipsilateral side as the lymph node aspiration using an intra-dermal 1.2-mm silicon needle as per intra-dermal injection SOP.

### Criteria for discontinuing or modifying allocated interventions {11b}

There are no plans to modify or permit modification of allocated interventions. The intervention will not be administered if the TolDC_CitPep_ do not meet stringent release criteria.

### Strategies to improve adherence to interventions {11c}

The intervention is administered as a single dose in a clinical research facility. It is felt unlikely that a participant would not attend for administration having undergone leukapheresis.

### Relevant concomitant care permitted or prohibited during the trial {11d}

Any medication or concomitant care not specifically listed is presumed to be permitted.

Permitted concomitant care:Permitted treatments for RA include methotrexate, sulfasalazine, azathioprine, hydroxychloroquine, abatacept, rituximab (last dose > 6 months ago), TNF-alpha inhibitors, and IL6 receptor antagonists, alone or in combination, at a stable dose for at least 4 weeksAnticoagulants unless these are, in the view of the investigator, likely to interfere with study procedures and cannot be interrupted

Prohibited concomitant care:Glucocorticoids (apart from topical, intra-nasal, inhaled)Janus kinase inhibitorsLeflunomideLive, attenuated vaccines within 2 weeks of and non-live vaccines within 1 week of the baseline visit

### Provisions for post-trial care {30}

Any unexpected or abnormal test results will be discussed with the participant and any necessary follow-up arranged with their rheumatologist, GP or another specialist. Participants will continue to access their usual health practitioners in the normal way throughout and after the study.

No additional TolDC product will be made available post-trial.

NHS indemnity for clinical trials will apply for clinical negligence that harms individuals towards whom the NHS has a duty of care.

### Outcomes {12}

#### Primary Endpoint/Outcome

There is currently no agreed biomarker for tolerance induction. Pragmatically, we shall seek evidence of favourable immunomodulation by selecting from a variety of different modalities including:Increase in proportional abundance of regulatory T cells in peripheral blood by high dimensional cytometryInduction or increase in Interleukin-10 production in peripheral blood mononuclear cells (PBMCs) following citrullinated peptide stimulation, using ELISpot or intracellular flow cytometryReduction in interferon gamma production in PBMCs following citrullinated peptide stimulationChange in proliferative response of PBMCs to citrullinated peptide stimulation, combined with phenotypic (surface marker, cytokine production) correlationA reduction in ACPA titre or diversity of ACPA specificitiesChanges in circulating cytokine levels

#### Secondary Endpoints/Outcomes

Secondary outcome measures for the study are:Change in ACR 20, 50 and 70, DAS-28, and components thereof at weeks 1, 3, 6 and 12 compared to baselineNumber of reported AEs. AEs will be collected at each timepoint (baseline, 1, 3, 6 and 12 weeks) from clinical assessment and routine blood testingParticipant reported acceptability of the TolDC_CitPep_ product and study-related procedures including leukapheresis and mode of administration. Data will be collected at the 12-week visit via the Participant Acceptability questionnaire

#### Exploratory Endpoint/Outcome Measures

Exploratory outcome measures for the study are:Enumeration and phenotypic analysis of autoreactive T cells by major histocompatibility complex class II tetramer stainingSingle cell RNA sequencing of peripheral blood T cells and lymph node aspiratesPotential associations between immune modulation (as defined by primary outcome measures) and evidence of efficacy (as defined by secondary outcome measures) for (1) the different routes of TolDC_CitPep_ administration (intra-articular, intra-dermal and intra-nodal) and (2) the different doses of TolDC_CitPep_ administered via the intra-nodal route (10^5^ and 10^7^)Comparison of (1) the different routes of TolDC_CitPep_ administration (intra-articular, intra-dermal and intra-nodal) and (2) the different doses of TolDC_CitPep_ administered via the intra-nodal route (10^5^ and 10^7^), for evidence of immune modulation and potential efficacy

### Participant timeline {13}

The study flowchart (Fig. 1) outlines the participant journey through the study and the schedule of events (Fig. 2) outlines the activities at each study visit.

**Fig. 1 Fig1:**
[figure not shown]
Trial flowchart

**Fig. 2 Fig2:**
[figure not shown]
Schedule of events

Screening will take place between day − 150 and day − 10. If screening takes place between day − 150 and day − 39 then a secondary screening visit will occur between day − 38 and day − 10. This is to ensure that the participant remains eligible and to allow for safety blood sampling in line with leukapheresis and TolDC production facility SOPs.

After screening and randomisation (and leukapheresis for those receiving TolDC_CitPep_), participants will attend for baseline (day 0) clinical and immunological assessments. All participants will provide a blood sample and an ultrasound-guided fine needle aspirate from inguinal lymph nodes. These blood and lymph node aspirate samples will contribute to the immunological endpoints described above. Participants in intervention arms will then receive TolDC_CitPep_ at the allocated dose and via the allocated administration route.

Participants will be followed up on four occasions at 1, 3, 6 and 12 weeks after the baseline visit. Clinical assessment and blood sampling will take place at each visit. At the week 1 follow-up visit, all participants will undergo a second lymph node ultrasound-guided fine needle aspirate.

If, during the follow-up period, a participant suffers deterioration in their arthritis symptoms, they will attend for a ‘flare visit’. A full clinical assessment will be performed and, if a flare of RA is diagnosed, the participant managed appropriately at the discretion of the investigator, according to standard care. If therapeutic intervention is required for the flare, final samples will be taken for immunological endpoints and the participant will exit the study.

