### Methods in analysis to handle protocol non-adherence and any statistical methods to handle missing data {20c}

An investigation of missing data will be undertaken to understand study withdrawals or missing appointments and whether these could be related to baseline factors or AEs. Where data are incomplete, existing data will be used for all analyses. There will be no attempt to impute missing data.

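### Participants whose flare needs treatment leave the study and nothing is imputed, so later ACR, DAS-28 and acceptability results describe only those without a treated flare

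*Protocol article*

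**What the plan says.** Three parts of the protocol article act together.

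- **Exit rule** (Participant timeline {13}, text below Fig. 2). Visits are planned as follows: "Participants will be followed up on four occasions at 1, 3, 6 and 12 weeks after the baseline visit". A flare visit is provided for participants whose arthritis worsens: "A full clinical assessment will be performed and, if a flare of RA is diagnosed, the participant managed appropriately at the discretion of the investigator". Then: "If therapeutic intervention is required for the flare, final samples will be taken for immunological endpoints and the participant will exit the study".
- **Outcomes** (Secondary Endpoints/Outcomes). ACR 20/50/70, DAS-28 and their components are due at weeks 1, 3, 6 and 12. For acceptability: "Data will be collected at the 12-week visit via the Participant Acceptability questionnaire". Treated flare is not listed as a primary, secondary or exploratory outcome.
- **Missing data** (section {20c}). "Where data are incomplete, existing data will be used for all analyses. There will be no attempt to impute missing data". The same section promises to look at whether withdrawals and missed visits relate to baseline factors or adverse events.

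Statistical methods {20a} then sets out comparisons of each active arm with control, and of the active arms with each other, on primary and secondary outcomes, with 4 participants per arm. Retention section {18b} provides for routine clinical data after withdrawal and for an attempted week-12 contact to check for adverse reactions in those given the product. It does not say whether a flare exit counts as a withdrawal.

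**The concern.** A flare that needs treatment is an unfavourable clinical result, and the Background uses the absence of flare in the phase I study as evidence that the cell phenotype was stable. Here that result removes the participant from later clinical summaries. The missing values arise from worsening of the disease that ACR and DAS-28 measure, so they are related to the outcome. A summary of available values at weeks 6 or 12 then covers a selected group, and the selection is stronger in an arm with more treated flares. The arm concerned could be an active arm or control, so the distortion can run either way.

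Acceptability has a similar problem. Someone who exits before week 12 is not asked under the stated schedule, so the ratings come from participants without a treated flare.

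At stake are the descriptive comparison of routes and doses on clinical outcomes, and the reading of acceptability. Both are meant to inform later studies.

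**Working it through.** **Inputs from the document.** Five arms in equal allocation and 20 participants (Abstract, Sample size {14}); 4 per arm (Statistical methods {20a}). Check: 5 × 4 = 20, which agrees. No flare, response or dropout rate is given and there is no power calculation, so there is no such figure to reproduce. The rates below are assumptions.

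**Step 1: what remains after an exit.** Set the three rules side by side for a participant with a treated flare between weeks 3 and 6:

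- Weeks 1 and 3: ACR and DAS-28 observed and used.
- Flare visit: clinical assessment including the RA assessment (section {18a}), CRP and ESR (Table 2, Set 5), and final immunological samples.
- Weeks 6 and 12: no study assessment, no imputation, and no stated rule placing the flare-visit value at these visits.
- Acceptability at week 12: not collected.

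**Step 2: effect on an ACR20 rate.** Assume k of the 4 participants are responders who do not flare, and one non-responder has a treated flare. With all 4 counted and the flare taken as non-response, the rate is k/4. From available data it is k/3. The shift is k/3 − k/4 = k/12.

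| k | k/4 | k/3 | Shift (percentage points) |
|---|---|---|---|
| 0 | 0% | 0% | 0 |
| 1 | 25% | 33% | 8 |
| 2 | 50% | 67% | 17 |
| 3 | 75% | 100% | 25 |

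With two treated flares and k = 2, the rate goes from 2/4 = 50% to 2/2 = 100%.

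**Step 3: effect on a DAS-28 mean.** Suppose three participants have no change and the flaring participant's value is 1.2 units above baseline at the flare visit. With that value included, the mean change is 1.2/4 = 0.3. From those remaining it is 0.

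**Step 4: how often an arm would be affected.** If each participant independently has probability f of a treated flare before week 12, the chance that a given arm loses at least one is 1 − (1 − f)^4:

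- f = 5%: 1 − 0.95^4 = 18.5%
- f = 10%: 1 − 0.90^4 = 34.4%
- f = 20%: 1 − 0.80^4 = 59.0%
- f = 30%: 1 − 0.70^4 = 76.0%

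Expected losses among 20 are 20f, that is 1, 2, 4 and 6. Each loss is 1/4 = 25% of an arm.

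**Step 5: the primary outcome.** Research blood is taken at baseline and weeks 1, 3 and 6, and lymph node aspirates at baseline and week 1. An exit after week 6 costs no scheduled research sample, and an earlier exit still yields a final sample. One point is less clear: after screening, the NHS laboratory ACPA test is listed only at follow-up visit 4 (Table 2, Set 4). The flare set includes it only as a discretionary extra. The final research samples may allow ACPA to be measured, but this is not stated.

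**The case against.** The strongest defence is that the worsening is seen before the participant leaves. The flare visit gives joint counts, global assessments, CRP and ESR, so DAS-28 can be calculated. The missing-data rule uses existing data and does not exclude that visit. The study is exploratory, with no formal testing beyond exploring methods and variability. With 4 per arm, results shown in tables and graphs with a CONSORT diagram would make a lost participant visible. Adverse events are counted for everyone who consents, and nothing prevents a flare from being recorded as one. How flare exits enter ACR results is also commonly settled in the SAP, which is not shown, and a definition of non-response need not conflict with a ban on imputation.

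Much of this stands, and it limits the point. Several stronger readings are not supported:

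- A reader might infer that everyone who flares is dropped. Only a flare needing therapeutic intervention leads to exit, and data up to and including the flare visit are kept.
- A reader might infer that the primary outcome is compromised. The final samples largely protect it.
- A reader might infer that every flare shifts the response rate by at least 17 points. That holds only for k = 2 or 3; for k = 0 nothing moves.
- A reader might infer that flare exits get no week-12 safety contact. Section {18b} places the contact in the paragraph on withdrawal but does not exclude them; it is unclear, not absent.
- A reader might infer a calculable understatement of variability for the next trial. That needs a model in which the worst changes are never observed, and the flare visit observes them.

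The defence does not remove two things. The article fixes an available-data rule for all analyses without saying how a flare-visit value counts at later visits. And an SAP cannot recover a questionnaire that was never given.

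**Conclusion.** The point holds at moderate severity, for secondary and descriptive outcomes. As written, ACR and DAS-28 summaries at visits after an exit, and all acceptability results, describe only participants without a treated flare. Comparisons between arms at those visits can therefore favour an arm with more treated flares.

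For one treated flare in an arm of 4, the ACR20 shift is 0 to 25 percentage points for k = 0 to 3. This assumes that the responders do not flare and that a treated flare counts as non-response. The number of such exits is unknown, because the document gives no flare rate. With no confirmatory test planned, no error rate is affected; the harm is to how the arms are described and compared.

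**What to change.** Leave clinical management of flares as it is and change only the data rules:

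1. Tabulate flare requiring treatment by arm as a clinical outcome.
2. Amend section {20c} so that participants who exit for a treated flare count as ACR non-responders at later visits. Present DAS-28 with the flare-visit value, which is already collected, included.
3. Give the acceptability questionnaire at exit or withdrawal as well as at week 12.
4. State in section {18b} that the week-12 adverse-reaction contact also applies to flare exits.

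Continued study DAS-28 assessment after exit is not requested, because those values would reflect the flare treatment as well as the allocated arm.

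The cost is a wording change in the protocol, matching text in the SAP, and a few extra questionnaires and contacts. Response rates may come out slightly less favourable. Items 3 and 4 are the urgent ones, since data not collected at exit cannot be obtained later; items 1 and 2 use data already planned.
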